**Table 1.3-2 Schedule of data collection and monitoring for participant (infant)**

| Working item                                                 | At the termination of pregnancy (delivery) | Day 3 after birth ( $\pm$ 1 day) | Day 7 after birth ( $\pm$ 3 days) | Day 28 after birth † ( $\pm$ 2 days) | postmenstrual age of 36 weeks # ( $\pm$ 2 days) | At discharge of infant ( $\pm$ 7 days) | At the cancelation of participation in the trial a |
|--------------------------------------------------------------|--------------------------------------------|----------------------------------|-----------------------------------|-------------------------------------------------|------------------------------------------------------------|----------------------------------------|---------------------------------------------------------------|
| Umbilical blood gas analysis                                 | X                                          |                                  |                                   |                                                 |                                                            |                                        |                                                               |
| Neonatal findings b                               | X                                          |                                  |                                   |                                                 |                                                            |                                        |                                                               |
| Apgar scores c                                    | X                                          |                                  |                                   |                                                 |                                                            |                                        |                                                               |
| Blood gas analysis d                              | X                                          | X k                   |                                   |                                                 |                                                            |                                        |                                                               |
| Hematological examination d                       | X i                             | X k                   |                                   |                                                 |                                                            |                                        |                                                               |
| Blood biochemical test d                          | X i,j                           | X k                   |                                   |                                                 |                                                            |                                        |                                                               |
| Culture of Ureaplasma spp. in throat e     | X                                          |                                  |                                   |                                                 |                                                            |                                        |                                                               |
| PCR for Ureaplasma spp. in throat e        | X                                          |                                  |                                   |                                                 |                                                            |                                        |                                                               |
| Culture of Ureaplasma spp. in ear cavity e | X                                          |                                  |                                   |                                                 |                                                            |                                        |                                                               |
| PCR for Ureaplasma spp. in ear cavity e    | X                                          |                                  |                                   |                                                 |                                                            |                                        |                                                               |
| Chest X-ray                                                  | X                                          |                                  | X l                    | X                                               | X l                                             |                                        |                                                               |

|                                                                 |   |   |   |   |                |   |   |
|-----------------------------------------------------------------|---|---|---|---|----------------|---|---|
| Total admission days                                            | X | X | X | X | X              | X |   |
| Presence/absence, kinds, and duration of respiratory management | X | X | X | X | X              | X |   |
| Presence/absence of BPD 36                           |   |   |   |   | X m |   |   |
| Presence/absence of BPD 28                           |   |   |   | X |                |   |   |
| Neonatal diseases f                                  | X | X | X | X | X              | X |   |
| Treatment for infant g                               | X | X | X | X | X              | X |   |
| Serious adverse events h                             | X | X | X | X | X              | X | X |

† Chief investigator (CI) or sub-investigator (SI) should perform data collection and monitoring at the one-month medical checkup, when the infant discharges within 28 days after birth.

# As for infants with birth at gestational ages <32 weeks PMA, the assessment of BPD36 should be performed at 36 weeks PMA or discharge to home, whichever comes first. As for infants with birth at gestational ages ≥32 weeks PMA, the assessment of BPD36 should be performed at ≥28 and <56 days postnatal age or discharge to home, whichever comes first.

a. CI or SI should investigate serious adverse events of the infant within 3 days after the cancelation of participation in this trial.

b. CI or SI should investigate the neonatal sex, birth weight (g), birth height (cm), head circumference at birth (cm), and presence/absence of small for dates, light for dates, large for dates, and heavy for dates.

c. The Apgar score should be recorded at 1 and 5 minutes after delivery.

d. The sampling of blood for the blood gas test is acceptable from either artery, vein, or capillary vessels.

e. CI or SI should not take biological specimens from the infant if the mother becomes complicated with COVID-19 infection.

f. CI or SI should investigate the presence/absence of intracranial hemorrhage (ICH), periventricular leukomalacia (PVL), respiratory distress syndrome (RDS), meconium aspiration syndrome (MAS), transient tachypnea in newborns (TTN), prolonged pulmonary hypertension (PPH), sepsis, necrotizing enterocolitis (NEC), local intestinal perforation, symptomatic patent ductus arteriosus (PDA), subglottic stenosis, laryngomalacia, and other upper airway diseases. CI or SI should also investigate the presence/absence of surgery for the infant. If the infant has any surgeries, CI or SI should investigate the surgical procedure, day of surgery, aim of surgery, and execution of intubation for the surgery.

g. CI or SI should investigate oxygen administration, intravenous/intratracheal administration of steroid, nitrogen monoxide inhalation, surfactant administration, caffeine administration, and azithromycin (AZM) treatment.

h. CI or SI should investigate serious adverse events of infants from the termination of pregnancy to discharge of the infant (or day of cancelation of participation in the trial for the mother).

i. The hematological examination and blood biochemical test at the termination of pregnancy for the infant are possible using cord blood.

j. The examination of IgM is performed only at delivery.

k. The blood gas test, hematological examination, and blood biochemical test should not be performed if the infant's birth weight is under 1,000 g.

l. Chest X-ray at 7 and 28 days after birth should be performed when needed.

m. As for an infant delivered at or after 32 weeks of gestation, the evaluation of BPD36 should be performed at 56 days after delivery or at discharge to home, whichever comes first.

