**7.5.3 TEST TO BE OBSERVED AND INVESTIGATED IN THE CHILDREN AND THE TIME OF IMPLEMENTATION**

---

(1) Neonatal findings

The Apgar score (1 and 5 minutes after birth), sex of the newborn, birth weight (g), birth height (cm), birth head circumference (cm), and neonatal growth level are entered into the eCRF.

Neonatal development is assessed as light-for-dates, small-for-dates, appropriate-for-dates, large-for-dates, or heavy-for-dates.

Time of implementation: At the end of pregnancy (at birth)

(2) Length of hospitalization of the child

The duration of the child's hospitalization (total number of days from the date of birth to the date of discharge or transfer) should be investigated and the results are entered into the eCRF. If the child's hospitalization continues at the 36 weeks and 0 days PMA (or at the follow-up after discontinuation), the child will be surveyed until discharge, if possible.

Time of implementation: at the end of pregnancy (at birth), 36 weeks 0 days PMA\*, at the time of discharge of the child

\*1: For children born at 32 or more weeks of gestation, the child is evaluated at day 56 or at discharge from the hospital, whichever occurs first.

(3) Respiratory management of the child

Investigate whether the child is on respiratory management and, if so, the duration and purpose of use by respiratory management method (invasive\*, non-invasive\*, other), and enter the information in the eCRF. If the child remains hospitalized at the 36 weeks and 0 days PMA (or at the time of cancellation of participation in the trial), the child will be surveyed until discharge, if possible.

Time of implementation: at termination of pregnancy (at birth), day 3, day 7, day 28\*, 36 weeks 0 days PMA\*, at discharge of the child

\*1: Ventilatory management by tracheal intubation

\*2: (Synchronized) nasal intermittent positive pressure ventilation ((s)NIPPV), nasal continuous positive airway pressure (NCPAP), nasal continuous positive airway pressure (NDPAP) with expiratory inspiration conversion, noninvasive neurally assisted ventilation

(NIV-NAVA), high flow nasal cannula (HFNC), positive deep breathing airway pressure (SiPAP), external Positive Airway Pressure (BiPAP)

\*3: For children discharged by day 28, evaluation is performed at the 1-month check-up.

\*4: For children born at 32 or more weeks of gestation, evaluate at day 56 or at discharge, whichever comes first.

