### 9.1 DEFINITION

#### 9.1.1 DEFINITION OF ADVERSE EVENTS

Adverse events in this study are defined as clinically problematic events among all unfavorable symptoms, signs, illnesses, and laboratory abnormalities that occur in subjects (mother, fetus) from the start of protocol treatment to the termination of pregnancy (or when study participation has discontinued). It does not matter if it has a causal relationship with protocol treatment. In infants, they are defined as clinically problematic events among all unfavorable symptoms, signs, illnesses, or abnormal laboratory abnormalities that occur between postpartum and the end of observation. However, IVH, PVL, RDS, meconium aspiration syndrome (MAS), TTN, PPHN, sepsis, NEC, which are defined as neonatal complications in this trial, localized intestinal perforation, and symptomatic PDA are not reported as adverse events in infants; but they are reported as serious adverse events if they fall under the definition of serious adverse events.

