### 9.5 COLLECTION AND TRACKING PERIOD

CI or SI should collect and record adverse events starting from the treatment start date. Clinical findings present on the date of consent are considered complications and not adverse events. However, exacerbations of complications are recorded as adverse events. As a rule, “disease etc.” and serious adverse events that are determined to have a causal relationship with the trial should be followed up to recovery or improvement as much as possible. Follow-up should be terminated when CI determines that further recovery is difficult or unfollowable due to death, disability, sequelae, etc. Non-serious adverse events that are not causally related to the trial are not specifically followed up in the trial, regardless of the outcome.

Regardless of the severity of adverse events, any adverse events that occur should be collected and recorded until the end of each subject's participation in the trial.

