## 10 CANCELTION AND COMPLETION

### 10.1 CANCELTION OF PARTICIPATION IN THE TRIAL

If the subject fails to comply with all study schedules, including efficacy and safety assessments, as well as discontinues protocol treatment for the following reasons (1. to 3.), participation in this trial should be canceled. This situation is called “cancellation of participation in the trial”.

If the protocol treatment is canceled before it has actually started, no observations should be performed, and appropriate treatment should be given so that the subject is not disadvantaged in

normal practice.

1. When the subject withdraws consent to participate in the study.
2. When “disease, etc.” that may lead to death or death occurs.
3. In addition, when the investigator determines that the risk of participating in the trial outweighs the benefits.

Basis for setting

- 1: Set from an ethical point of view.
- 2 – 3: Established from the viewpoint of subject safety.

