## 3. Safety analysis target population

All subject populations (mother, fetus/infant) who received at least one protocol treatment.

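### Note h closes infant SAE collection when the mother's participation is cancelled, in conflict with section 9.1.1, so infant harm can be under-counted

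*Protocol*

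**What the plan says.** Note h, printed under both Table 1.3-2 and Table 7.5-2, sets the window for infant SAEs: "from the termination of pregnancy to discharge of the infant (or day of cancelation of participation in the trial for the mother"). Note a under the same tables adds: "CI or SI should investigate serious adverse events of the infant within 3 days after the cancelation of participation in this trial". Section 9.5 gives a matching general end point: "any adverse events that occur should be collected and recorded until the end of each subject's participation in the trial".

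Other sections are wider. Section 9.1.1 defines infant adverse events as those "that occur between postpartum and the end of observation" and does not mention the mother's cancellation. Section 7.5.3 (3), on respiratory management of a child still in hospital at 36 weeks 0 days, continues: "or at the time of cancellation of participation in the trial), the child will be surveyed until discharge, if possible". Section 7.5.3 (4) makes the same provision for oxygen.

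Section 10.1 lists three reasons for cancellation:
- item 1: "When the subject withdraws consent to participate in the study";
- item 2: when a 'disease, etc.' "that may lead to death or death occurs" (section 9.1.4 reserves this term for events suspected to be caused by the trial);
- item 3: the investigator judges that risk outweighs benefit.

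Section 14.1 defines the safety set as "All subject populations (mother, fetus/infant) who received at least one protocol treatment". Section 14.2.4 D reports infant SAEs in that set as numbers, frequencies and 95% confidence intervals.

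**The concern.** The window opens at delivery and can close on a date that belongs to the mother. If she is cancelled during pregnancy, it closes before it opens. Items 2 and 3 of section 10.1 tie some cancellations to suspected harm or an unfavourable risk judgement, so the infants who drop out of view may differ from those who remain. They nevertheless stay in the population on which infant SAE frequencies are calculated.

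Safety is part of the primary objective (section 1.1). Section 2.1.3 asks for detailed study of azithromycin safety because dose and duration exceed those of earlier trials. Section 16.5 sets up no efficacy and safety evaluation committee. What is at stake is the infant safety summary, not the BPD comparison.

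**Working it through.** **The passages side by side**

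| Place | End of infant observation | Tied to the mother's cancellation? |
|---|---|---|
| Note h, Tables 1.3-2 and 7.5-2 | Discharge, or day of cancellation | Yes |
| Note a, same tables | One check, within 3 days after cancellation | Yes |
| Section 9.5 | End of each subject's participation | Yes, in effect |
| Section 9.1.1 | End of observation | No |
| Section 7.5.3 (3)-(4) | Discharge, if possible | Continues after it |

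The first three rows and the last two cannot all govern the same infant.

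**Length of the window**
- Cancellation before birth: note h gives no window. Note a reaches the infant only if birth falls within the 3 days.
- Cancellation on the day of birth at, say, 26 weeks: the 36-week assessment is (36 - 26) x 7 = 70 days away, and note a covers at most the first 3.

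**Size of the under-count**

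The protocol has no figure of its own to reproduce: it gives no cancellation rate and no infant SAE rate.

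Inputs:
- n = 50 per arm (section 5.2.1).
- c = 1 to 5 mothers per arm treated and then cancelled before birth (assumed).
- p = 20% to 60% true infant SAE risk (assumed).
- None of the c infants has an SAE recorded, and each stays in the denominator as event-free (assumed).

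Reported risk = p x (50 - c)/50. Shortfall = p x c/50.

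Example: p = 40%, c = 5 gives 0.40 x 45/50 = 36% reported, a shortfall of 4 points.

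| p | c = 1 | c = 3 | c = 5 |
|---|---|---|---|
| 20% | 0.4 | 1.2 | 2.0 |
| 40% | 0.8 | 2.4 | 4.0 |
| 60% | 1.2 | 3.6 | 6.0 |

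(Shortfall in percentage points.)

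If the cancelled infants carried twice the risk, q = 2p capped at 100%, the shortfall would be q x c/50. At c = 5 that is 4, 8 and 10 points for p = 20%, 40% and 60%. Nothing in the protocol supports or rules out the doubling.

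**The case against.** Several stronger readings are tempting, and the protocol does not support them.

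- **That collection stops dead on the day.** Note a adds a check within 3 days. This stands, though it is small against a neonatal stay.
- **That the loss falls exactly where the mother had a dangerous drug reaction.** This is one of three cancellation reasons. After consent withdrawal, stopping may be unavoidable. Under section 6.2.6, a woman who only stops treatment stays under observation. Item 2 can also concern the fetus, and after an intrauterine death there is no later infant to observe.
- **That infant SAEs alone are cut.** BPD and neonatal diseases also have no mark in the cancellation column of the infant schedule. The continued survey in section 7.5.3 (3)-(4) is only if possible and, after cancellation, concerns a child already in hospital. It shows that record review after cancellation is feasible, but does not itself cover a cancellation in pregnancy. The continued maternal follow-up in the notes to Table 1.3-1 covers only the events that caused the cancellation.
- **That a later death or serious illness would certainly miss the tables.** Section 9.1.1 has no maternal cut-off, and section 9.6.1 asks for infant SAE reports without stating one. The text is inconsistent, so the loss is possible rather than settled.
- **That unobserved infants will be counted as event-free.** Section 14.1 keeps them in the set, but the protocol does not say how an infant with no observed window is tabulated. An analysis plan may do so.
- **That the less tolerated arm would look safer, or the sign of the difference reverse.** This needs unequal, harm-driven cancellations and assumed risks. Section 14.2.4 D plans no between-arm difference for infant SAEs.

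These points narrow the concern but do not remove it. Handling of the denominator can be left to an analysis plan. SAEs that were never collected cannot be recovered by one.

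**Conclusion.** Note h and section 9.5 set a narrower infant SAE window than section 9.1.1, and where cancellation precedes birth the narrower one is essentially empty. Infant SAEs can therefore be under-counted among infants who may not be a random subset. The size cannot be derived from the protocol. Under the assumptions shown, it is about 0.4 to 6 points per arm, and up to 10 if the lost infants have doubled risk. With few cancellations it would be near the lower end.

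The primary outcome is not threatened by this route, because section 14.2.2 counts a missing primary outcome as an event in the full analysis set. The change is worth making because safety is a stated aim and the gap lies in data collection.

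**What to change.** Reconcile note h in both tables, and section 9.5, with section 9.1.1:

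- After cancellation under section 10.1 items 2 and 3, collect infant SAEs and deaths to discharge by record review.
- After withdrawal of consent, do so only where the mother permits use of the infant's record.
- Report by arm the number of infants whose SAE window was not fully observed.

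This concerns data collection only. It leaves the cancellation criteria and clinical care as they are.

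The cost is a protocol amendment with committee review, possibly a line in the consent form, and record review for a few infants. No extra tests or visits are needed. This edition is dated November 2023 and registration was expected to close in March 2024, so the sponsor would need to check whether the existing consent covers women already enrolled.

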## 2 BACKGROUND

### 2.1 BACKGROUND

#### 2.1.1 PRETERM PREMATURE RUPTURE OF FETAL MEMBRANE (PPROM) OCCURRING AT <28 WEEKS OF GESTATION AND BRONCHOPULMONARY DYSPLASIA (BPD)

Preterm premature rupture of the membranes (pPROM) is defined as PROM occurring at <37 weeks of gestation.

In Japan, pPROM accounted for 28.7% and 28.1% of very preterm births of less than 28 and 32 weeks of gestation, respectively. Therefore, it is estimated that about 700 children are born very preterm each year as a result of pPROM and about 1,700 children are born extremely preterm each year.

There are many kinds of neonatal complications in infants born to women with pPROM: pulmonary hypoplasia due to oligohydramnios, bronchopulmonary dysplasia (BPD), dry lung syndrome, amniotic band syndrome, neonatal asphyxia, persistent pulmonary hypertension in the neonate (PPHN), intraventricular hemorrhage (IVH), acute inflammatory disease due to amniotic infection such as sepsis, pneumonia, and meningitis, fetal inflammatory response syndrome such as chronic lung disease, necrotizing enterocolitis (NEC), periventricular leukomalacia (PVL), and long-term neurodevelopment impairments.

BPD is defined as respiratory distress symptoms that require oxygenation persisting beyond day 28, after neonatal respiratory compromise has abated or beginning soon after the neonatal respiratory compromise. The severity of BPD is classified by National Institute of Child Health and Human Development (NICHD) as mild, moderate, or severe depending on the infant's oxygen use at postmenstrual age (PMA) of 36 weeks, the oxygen concentration administered, and whether positive pressure ventilation. BPD is a frequent complication that occurs in approximately 50% of very low birth weight infants. The earlier the week of gestation, the higher the rate of BPD complications. Recent analyses using the Neonatal Research Network database Japan (<http://plaza.umin.ac.jp/nrndata/>) reported that the incidence of BPD36 in surviving discharged children delivered at 22, 23, 24, 25, 26, 27, 28, 29, and 30 weeks of gestation was 76, 72, 67, 58, 50, 41, 32, 24, and 17%, respectively. Because these data included infants not complicated with pPROM, we estimate that the incidence of BPD36 in infants with pPROM may be higher.

Some infants with moderate/severe BPD36 show continued respiratory failure beyond the neonatal period, and they need long-term oxygen and/or respiratory support. After school age, central nervous system effects are also seen, including decreased brain capacity and lower IQ in cognitive and language development. Although much research and treatment has been done, the incidence is still high, around 50%, and has a significant impact on the prognosis of very low birth weight infants.

It has been reported that pPROM is an independent risk factor for BPD. We analyzed 55 pregnant women with singleton pregnancy who had pPROM at <28 weeks of gestation, and delivered between 22 and 31 weeks of gestation, and we investigated the association between pPROM and the subsequent occurrence of short- and long-term prognoses; perinatal death occurred in 13% (intrauterine death: 6%, early neonatal death: 7%), pulmonary hypoplasia in 14%, respiratory distress syndrome (RDS) in 56%, transient tachypnea of newborn (TTN) in 42%, NEC

in 6%, IVH in 10%, PVL in 10%, sepsis in 4%, BPD at 28 days of life (BPD28) in 72%, and BPD36 in 60% .

Since supportive care such as oxygen therapy is the only treatment for BPD, the prevention of BPD is strongly desired. To this end, it is very important for women with pPROM occurring at <28 weeks of gestation to receive appropriate antibiotics, and to prolong the pregnancy period.

